##### Luteinized granulosa cell gene expression analysis

Human luteinized granulosa cells (GC) from placebo- and vitamin D- supplemented patient groups will be isolated from the discarded follicular fluid post oocyte retrieval according to standard protocols [15]. Briefly, cells in follicular fluid will be isolated by initial centrifugation of the pool of follicular fluid (2000×g for 10 min) followed by gradient separation at density of 1.077 g/mL (Lymphoprep™, STEMCELL Technologies, Vancouver, Canada). Following the gradient centrifugation (1700×g for 20 min), three layers will emerge: a top layer containing the follicular fluid, a bottom layer containing erythrocytes and the middle layer containing mononuclear cells. The mononuclear middle layer will be collected and supplemented with 3 ml of RPMI 1640 medium containing 10% fetal bovine serum. To eliminate the macrophages, the mononuclear cell suspension will be incubated in a Petri plate, at 37 °C for 15 min. It is expected that, while macrophages will adhere to the plastic during this time frame, luteinized GCs and lymphocytes will not. An additional step to separate GCs from lymphocytes will be performed by maintaining the cell suspension for 24 h at 37 °C under standard culture conditions. Due to their physical properties, lymphocytes, in contrast to GCs, cannot attach to plastic, thus, allowing an effective segregation of the two cell types. GCs will be lysed using the RLT buffer (QIAGEN) and total RNA will be sentd for RNAseq analysis. TruSeq Stranded Total RNA Library Prep Kit will be used for library preparation and sequenced on an Illumina HiSeq2500 Rapid Run System, generating pair-end 50 base-pair reads (140 M reads on average per sample). Transcript abundance will be estimated with Kallisto [16] and differentially expressed (DE) genes will be identified using DeSeq2 R package [17] and a corrected *p*-value < 0.05. The DE genes that will emerge from RNAseq analysis between placebo and vitamin D-supplemented groups, will be validated with RT-PCR using SYBR green system, QIAGEN pre-validated, ready-to-use primer sets and QIAGEN real-time PCR cycler, the Rotor-Gene Q. A new cohort of samples will be employed for the validation. Western blotting analysis will be used to confirm the changes in gene expression at the protein level.

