Oocytes cannot be directly tested for molecular analyses. However, the evaluation of the cumulus and granulosa cells of the ovarian follicle could indirectly reveal the quality of the corresponding oocytes. The gene expression profile of cumulus-oocyte-complexes has been suggested to predict which embryos have the best chance of implanting in the uterus. In particular, the expression of COX20, BMP15 and GDF9 has been associated with the establishment of pregnancy or live birth. Other possible potential genes of interest but with less consistency among studies include GREM1, HAS2, VCAN, PTGS [9, 10].

Endometrial samples can conversely be obtained prior to initiate the IVF cycle and can thus be directly studied without interfering with the procedure. Of interest here is that the endometrium and the early pregnancy decidua also express VDR and could be other important targets of vitamin D. In a previous study from our group, vitamin D was shown to modulate the expression of genes important for embryo receptivity and to interact with the local cytokines in human endometrial cells [11].

In the present study the following hypotheses will be tested: 1) 25-hydroxyvitamin D [25(OH)D] deficiency negatively affects pregnancy rates in IVF cycles with an effect mediated through endometrial receptivity and/or oocyte embryo quality; 2) Vitamin D supplementation and restoration of adequate vitamin D levels may actually improve the prognosis of infertile women undergoing IVF procedures. The absolute magnitude of the benefit deemed to be clinically relevant in terms of cumulative clinical pregnancy rate is considered 10% (from 20 to 30%); 3) The molecular profiles of endometrium, follicular fluid and cumulus cells are modified in vitamin D-supplemented women with respect to molecules known to be associated with IVF outcomes and embryo implantation process.

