**Fig. 1 Fig1:**
[figure not shown]
Schedule of enrolment, interventions and assessments of the SUNDRO trial

#### Experimental design aim 2

In order to investigate whether vitamin D supplementation might improve clinical and embryological parameters, we will use our electronic dataset to compare with appropriate statistical tests all of the variables that are routinely collected in IVF cycles. The main variables that we will consider in order to discover possible effects of vitamin D supplementation on the clinical outcome of the IVF cycle are: rate of cancelled cycles, number of available oocytes, units of FSH administered per retrieved oocyte (they are related to the rate of appropriate response of the patients to the stimulation protocol), number of good quality embryos on the day of embryo transfer as evaluated according to the Istanbul Consensus (it is related with the quality of gametes) [14], implantation rate of transferred embryos (it is related to the quality of embryos and endometrium), delivery rate and obstetric outcomes.

#### Experimental design aim 3

A subgroup (*n* = 50) of good-prognosis cases and controls will be recruited among randomized patients for collection and analysis of biological samples as described below.

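### The IVF-related genes named in the Background get no test of their own in the ovarian cells, only a transcriptome-wide screen, which costs power for hypothesis 3

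*Protocol article*

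**What the plan says.** Hypothesis 3, at the end of the Background, is that supplementation changes the molecular profiles of endometrium, follicular fluid and cumulus cells "with respect to molecules known to be associated with IVF outcomes and embryo implantation process". The hypothesis names no gene. Earlier in the Background the authors write that "the expression of COX20, BMP15 and GDF9 has been associated with the establishment of pregnancy or live birth", and add: "Other possible potential genes of interest but with less consistency among studies include GREM1, HAS2, VCAN, PTGS". That makes seven named genes in two tiers.

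The section on luteinized granulosa cell gene expression names none of them. There, "total RNA will be sentd for RNAseq analysis", and "differentially expressed (DE) genes will be identified using DeSeq2 R package [17] and a corrected *p*-value < 0.05". The next step is stated as a rule: "The DE genes that will emerge from RNAseq analysis between placebo and vitamin D-supplemented groups, will be validated with RT-PCR". On the samples for that step: "A new cohort of samples will be employed for the validation".

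The other two molecular sections work from named molecules. Follicular fluid content compares BMP-15 and GDF-9 proteins between arms. Endometrial secretion pattern measures a listed panel chosen for its role in implantation.

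The size of the sub-study is given under Experimental design aim 3 as a subgroup (n = 50) "of good-prognosis cases and controls will be recruited among randomized patients for collection and analysis of biological samples".

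**The concern.** A hypothesis about a short list of known molecules calls for a test of that list at its own error rate. In the ovarian cells, each named transcript must instead clear a threshold set by correction over every transcript sequenced. A named gene that truly changes but misses that threshold has no stated route to a candidate-level test or to RT-PCR.

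What is at stake is power on the genes that motivated the molecular work. Sequencing will measure all seven, so the information will exist, but the written rule makes poor use of it. The genes carried forward will be whichever emerge from the screen, and these need not include any that the Background links to pregnancy.

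**Working it through.** **The plan's own figures.** No power, effect size or variability is stated for the molecular sub-study, so there is nothing to reproduce there. The only computed sample size is for the primary outcome. For 20% against 30%, two-sided 0.05 and 80% power, the usual formula gives 294 per arm against the stated 300. It is sound and does not bear on this point.

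**Which named genes have a directed test**

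| Named in the Background | Directed test as transcript | Directed test as protein |
|---|---|---|
| BMP15, GDF9 | none | follicular fluid |
| COX20 | none | none |
| GREM1, HAS2, VCAN, PTGS | none | none |

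**Inputs for the power comparison**
- From the protocol: corrected p < 0.05; seven named genes; n = 50, read as 25 per arm (50 in total) or 50 per arm.
- Assumed: a two-sided two-sample t test on a roughly normal expression scale, standing in for DESeq2; Benjamini-Hochberg at 5% as the correction; the same standardised difference d for all changed genes.
- Share of genes changed, π: assumed 0.5% to 5%. The range is borrowed from the Background's figure for the part of the genome the vitamin D receptor may regulate. It is not an estimate of the share changed in these cells.

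**Formulas**
- Power at per-gene level a: P(a) = Pr(T > t(1 − a/2; 2n − 2)), where T is noncentral t with 2n − 2 degrees of freedom and noncentrality d·√(n/2).
- Seven-gene family: a = 0.05/7 = 0.0071.
- Screen: the largest a that satisfies a = 0.05 × [(1 − π)·a + π·P(a)].

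**One case in full.** Take n = 25 per arm, d = 1.0 and π = 0.5%. The noncentrality is √12.5 = 3.54. The screen equation solves at a = 0.0000572 with P = 0.2175. Check: 0.05 × (0.995 × 0.0000572 + 0.005 × 0.2175) = 0.05 × 0.001144 = 0.0000572. Screen power is therefore 22%. At a = 0.0071 the same difference has 76% power.

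**Results**

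| Per arm | Difference (SD) | Screen, π = 0.5% | Screen, π = 5% | Seven-gene family |
|---|---|---|---|---|
| 25 | 0.8 | 2% | 21% | 51% |
| 25 | 1.0 | 22% | 57% | 76% |
| 25 | 1.2 | 55% | 83% | 92% |
| 50 | 0.5 | 1% | 12% | 41% |
| 50 | 0.7 | 27% | 60% | 77% |
| 50 | 0.8 | 51% | 80% | 89% |
| 50 | 1.0 | 87% | 97% | 99% |
| 50 | 1.2 | 98% | >99% | >99% |

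The screen is never ahead. The gap is wide at 25 per arm or with moderate differences, and nearly closes at 50 per arm once the difference reaches 1.0 SD. Bonferroni is the conservative choice for the family; Holm or Benjamini-Hochberg within the seven would do at least as well.

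**The case against.** The strongest reply is that Aim 3 as a whole is not blind to candidates. Two of the three compartments in hypothesis 3 are tested on named molecules, and two of the three leading candidates are measured as proteins. A reader might infer from the granulosa section that the plan fails to test hypothesis 3 at all. The follicular fluid and endometrial sections rule that out, and the point is confined to gene expression in the cells.

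A reader might also infer that an empty screen would be reported as no molecular effect. The protocol nowhere says so, and its Discussion calls the molecular results preliminary.

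Third, the seven genes are background literature, four of them flagged as less consistent. That literature concerns cumulus-oocyte complexes, while the cells sequenced are luteinized granulosa cells from pooled follicular fluid. This stands as a reason not to give the seven priority over the screen. It is no reason to leave them without a test, since the protocol offers them as the markers of interest.

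Fourth, an unbiased screen with validation in fresh samples is a coherent discovery design, and a candidate family could be added in an analysis plan. Both are true. But the published section already fixes the threshold and the rule for what is validated, and that rule selects on the screen alone.

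**Conclusion.** The point holds in limited form. In the ovarian cells, the transcripts named in the Background are tested with less power than hypothesis 3 allows: 22-57% against 76% at 25 per arm and 1.0 SD, and 27-60% against 77% at 50 per arm and 0.7 SD.

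It is tempting to say flatly that these genes are tested with little power, for instance by treating the correction as Bonferroni over some 15,000 genes. At 25 per arm and 1.0 SD that gives 7%. The documents do not support this as a general statement. It presumes almost no true changes, and with 50 per arm and large differences the screen does well. Effect size, share of changed genes, correction method and the meaning of n = 50 are all unstated, so the figures above are a range under assumptions and not a property of the plan.

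Severity is low. The aim is secondary and mechanistic, and the primary result is untouched.

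**What to change.** In the section on luteinized granulosa cell gene expression:

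1. List the seven genes named in the Background as a pre-specified candidate family, fixed before expression data are linked to allocation.
2. Test them between arms in the same RNAseq data, with correction within the family (Holm or Benjamini-Hochberg, for example), and report all seven with estimates and intervals whatever the screen shows.
3. Keep the transcriptome-wide DESeq2 screen, and its validation in new samples, as the discovery analysis alongside.
4. Optionally, add the candidates to the RT-PCR set irrespective of the screen.
5. Say whether n = 50 is the total or the number per arm.

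Items 1 to 3 and 5 cost a paragraph of wording and use data already planned. Item 4 costs a few more primer sets and some bench work; the protocol does not give the size of the validation cohort, so this cannot be put more exactly.

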##### Follicular fluid content

BMP-15 and GDF-9 are currently regarded as the best candidate molecules responsible for oocyte regulation of cumulus cell expansion during ovulation. Follicular samples from both groups of women will be retrieved via transvaginal route under ultrasound guidance. Follicular fluids will be centrifuged at 1000×g for 10 min to remove cellular components; the clear supernatant will be divided into aliquots and frozen at − 80 °C until further use. Prior to processing, the follicular fluids will be centrifuged and filtered on Millipore filter to remove precipitates. A chemiluminescent assay will be used to compare BMP-15, GDF-9 and 25(OH) D levels in follicular fluid of women treated or not with vitamin D supplementation.

##### Endometrial secretion pattern

Endometrial secretions from both groups of women treated or not with vitamin D supplementation will be aspirated using a catheter during the secretory phase of the menstrual cycle prior to frozen embryo transfer: a multiplex immunoassay will be performed to compare the cytokine profile. Interleukin (IL)-1ß, IL-10, IL-12, IL-15, IL-17, tumor necrosis factor (TNF)-α, eotaxin, glycodelin A, granulocyte colony-stimulating factor, monocyte chemotactic protein-1, vascular endothelial growth factor, interferon-gamma will be analysed given their known involvement in human embryo implantation.

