**Discussion:**

The primary aim of the study is the cumulative clinical pregnancy rate per oocyte retrieval. Clinical pregnancy is defined as the presence of at least one intrauterine gestational sac with viable foetus at first ultrasound assessment (3 weeks after a positive human chorionic gonadotropin [hCG] assessment). Secondary outcomes include: 1) clinical and embryological variables; 2) oocyte and endometrium quality at a molecular level. To investigate this latter aspect, samples of cumulus cells, follicular and endometrial fluids will be obtained from a subgroup of 50 age-matched good-prognosis cases and controls.

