### Participants

Inclusion criteria of women will be as follows: indication to IVF, age 18–39 years, less than 3 previous IVF attempts, body mass index (BMI) 18–25 kg/m^2^.

Exclusion criteria will be as follows: patients with anti-mullerian hormone serum level < 0.5 ng/ml, IVF cycle using frozen embryos/oocytes, vitamin D contraindications/side effects for consumption of vitamin D (high blood calcium levels or conditions that can lead to high calcium levels such as sarcoidosis, tuberculosis, parathyroid disease).

Eligible women will be informed on the study design and those agreeing to participate will sign an informed consent and will provide a blood sample for 25(OH) D assessment. Those with a serum level < 30 ng/ml will be randomized.

A CONSORT flow diagram of the study protocol is provided as an additional figure (see Additional file 1).

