### Interventions

#### Experimental design aim 1

Recruited women will be given the drug (either 600,000 IU of 25-OH-vitamin D or placebo in a single oral administration) at the time of randomization, thus 2–12 weeks prior to oocyte retrieval and managed according to a standardized clinical protocol of ovarian stimulation with in vitro fertilization (fresh cycle). Administration of the drug/placebo will be performed by the physician in order to guarantee a compete adherence to the protocol. No dose changes are foreseen. Patients will be asked to avoid further consumption of vitamin D after randomization.

Women whose cycle will be cancelled will not be excluded (intention to treat analysis). A specific software will establish the randomization list. Sun exposure during the study period will be recorded but it will not be a reason for drop-out. Serum 25-OH-Vitamin D will be reassessed at the time of hCG administration or, if the cycle will be cancelled, at the time of the decision to interrupt the treatment. The quantitative detection of total serum 25(OH) D levels will be performed using a commercially available kit based on a chemiluminescence technology (DiaSorin) with intra- and interassay coefficients of variations equal to 10 and 15%, respectively.

Patients will be treated according to standard IVF protocols as described elsewhere [12, 13]: since neither the clinicians nor the recruited women will be aware about vitamin D dosage, clinical management of ovarian stimulation will not be conditioned by the study.

In case of supernumerary oocytes or embryos deriving from the fresh cycle, the subsequent embryo transfer using thawed embryos or oocytes will be considered for the study outcome if performed within 4 months from oocyte retrieval and 25(OH) D serum levels will be reassessed.

Serum hCG assessment to detect pregnancy will be performed at + 14/+ 16 days after hCG administration. If positive, women will undergo a transvaginal sonography 3 weeks later.

Clinical pregnancy (primary outcome) is defined as the presence of at least one intrauterine gestational sac with viable foetus.

Dates of the study: 27/06/2016–26/06/2019

A schedule of enrolment, interventions and assessments of the study protocol is reported in Fig. 1.

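### Aim 3 samples endometrial fluid only in women who go on to a frozen embryo transfer, so randomisation does not protect that comparison between arms

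*Protocol article*

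**What the plan says.** Aim 3, one of the three main aims, compares cumulus or granulosa cells, follicular fluid and endometrial fluid between treated and untreated women. Under Experimental design aim 3 the subgroup of 50 is described as "of good-prognosis cases and controls will be recruited among randomized patients". The Abstract calls it "a subgroup of 50 age-matched good-prognosis cases and controls"; age-matching is not mentioned again in the Methods.

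Endometrial secretion pattern sets the sampling point: "during the secretory phase of the menstrual cycle prior to frozen embryo transfer". The Background motivates the work differently: "Endometrial samples can conversely be obtained prior to initiate the IVF cycle and can thus be directly studied without interfering with the procedure".

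Two other sections determine who can reach that sampling point. Participants lists as an exclusion "IVF cycle using frozen embryos/oocytes", and Interventions describes the randomised cycle as fresh. A later transfer arises only "In case of supernumerary oocytes or embryos deriving from the fresh cycle", and it counts towards the primary outcome "if performed within 4 months from oocyte retrieval".

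**The concern.** Having a sample depends on what happened in the fresh cycle, after dosing. If vitamin D changes who gets that far, the sampled women in the two arms differ for reasons unrelated to any effect on the endometrium. The Background presents biological evidence from randomised trials as the gap to be filled, and its third hypothesis is that molecular profiles are modified in supplemented women. On this schedule, a difference in the cytokine panel could reflect supplementation, selection or both. An absent difference would be equally ambiguous. An analysis method could address this only with assumptions that randomisation does not supply.

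**Working it through.** The plan gives no figure for this point: no share of women expected to reach a frozen transfer, and no derivation of the subgroup of 50. The check is therefore mainly a tracing of the pathway, followed by two illustrations.

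**1. Steps from randomisation to an endometrial sample**

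| Step | Source | Could treatment change it? |
|---|---|---|
| Fresh cycle not cancelled, oocytes retrieved | Interventions | Yes: cancellation is an Aim 2 variable |
| Surplus oocytes or embryos | Interventions | Yes: oocyte number and good-quality embryos are Aim 2 variables |
| No ongoing pregnancy from the fresh cycle, or no fresh transfer | Inferred from practice | Yes: implantation is an Aim 2 variable and clinical pregnancy is the primary outcome |
| Frozen transfer undertaken | Endometrial secretion pattern | Follows from the steps above |

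Granulosa cells and follicular fluid are taken at oocyte retrieval, so they need only the first step.

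**2. How large could the imbalance be? (illustration; the shares and the correlation are assumptions)**

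Let prognosis Z be standard normal, and let a woman reach frozen transfer when an index correlated ρ = 0.71 (1/√2) with Z exceeds a cut-off c. If a proportion p reach it, then c = Φ⁻¹(1 − p) and the mean of Z among those sampled is ρ·φ(c)/p:

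- p = 0.30: 0.7071 × 0.348/0.30 = 0.82
- p = 0.40: 0.7071 × 0.386/0.40 = 0.68
- p = 0.50: 0.7071 × 0.399/0.50 = 0.56
- p = 0.60: 0.7071 × 0.386/0.60 = 0.46

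Difference in mean prognosis, second arm minus first, from unrounded values:

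- 30% v 40%: −0.14 SD
- 40% v 50%: −0.12 SD
- 40% v 60%: −0.23 SD
- equal shares: 0 in this model

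A marker with correlation r to prognosis would shift by r times these values, with no effect of treatment on the endometrium.

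The sign should not be relied on. More surplus embryos in the treated arm would raise its share reaching frozen transfer. More fresh-cycle pregnancies would lower that share, and would remove women in whom implantation succeeded. The two routes oppose each other, and the documents do not say which dominates.

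**3. Does the Background's rationale fit the schedule?**

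The Background describes sampling before the IVF cycle; the Methods sample after the fresh cycle. Interventions puts retrieval 2 to 12 weeks after dosing, and the Discussion says adequate levels last up to 90 days. At the 4-month limit, with 30.4-day months:

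- earliest retrieval: 14 + 122 = about 136 days after dosing
- latest retrieval: 84 + 122 = about 206 days after dosing

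Earlier transfers could fall within 90 days. The 4-month limit is stated for the primary outcome, not for sampling. The two accounts of timing therefore describe different exposure conditions.

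**The case against.** The best defence is one of scope. Aim 3 is secondary and mechanistic, the Discussion already calls its results preliminary, only one of three sample types is affected, and the primary analysis is untouched. All of that stands. It limits the importance of the point, but it does not make the endometrial comparison a randomised one.

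Four stronger readings are tempting, and the documents do not support them.

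- **That age-matching must break the blind or cannot be done.** The pharmacy holds the codes and could form pairs. Samples could be matched after the permitted unblinding, and a common age band needs no allocation at all. Who matches, and when, is detail that an article may leave to the full protocol. Choosing randomised women on age, a baseline variable, does not by itself undo randomisation.
- **That the Background contradicts the Methods.** It says only that samples can be obtained before the cycle. That is a remark on feasibility; the Methods give the only schedule. The mismatch is between rationale and schedule.
- **That every sampled woman is a treatment failure.** A woman with frozen embryos and no fresh transfer has not failed one.
- **That the number of women sampled can be worked out.** The 20% and 30% in Sample size calculation are cumulative rates for the whole trial, not fresh-cycle rates in a good-prognosis subgroup. The article also does not say whether 50 is the number recruited or the number finally sampled.

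**Conclusion.** The point holds for endometrial fluid alone. As scheduled, that comparison is conditional on reaching a frozen transfer, a post-randomisation state that vitamin D is meant to influence, so a difference between arms cannot be read as a randomised effect of supplementation. The size and direction of any bias are unknown; 0.12 to 0.23 SD in prognosis is an illustration under assumed shares and an assumed correlation. The conclusion rests on two things: the article's own statement that frozen transfers come from surplus material of the fresh cycle, and the practical inference that women with an ongoing fresh-cycle pregnancy do not go on to one. The Background's rationale should be brought into line with the schedule.

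**What to change.** 1. Define good prognosis by baseline variables only, and select sub-study women blind to arm.
2. Replace the description as age-matched cases and controls with randomised arms, compared with adjustment for age.
3. Reconcile the Background's account of when endometrial samples are obtained with Endometrial secretion pattern.
4. If sampling stays before frozen transfer, state that the endometrial comparison is exploratory and conditional on reaching frozen transfer. Report by arm how many sub-study women were sampled and their baseline features, and do not present the result as a randomised effect of supplementation.

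These are changes of wording and reporting. The cost is a weaker claim for the endometrial result and possible small chance differences in age between arms, which the adjustment handles. Sampling at a point that every sub-study woman reaches would remove the condition, but it changes a procedure and its timing. That is a trade-off for the sponsor to weigh, not a matter of wording.
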